### Randomization

Assignment of schools to the control or intervention condition is carried out according to the International Council for Harmonisation guidelines [32] and performed by a researcher not involved in the day-to-day conduct of the trial. Schools are allocated to a single condition (cluster design) to avoid contamination and for administrative convenience [33]. A minimization approach [34,35] is used to ensure balance across conditions in terms of the Index of Community Socio-Educational Advantage level (<1000 vs ≥1000), gender mix (coeducational vs single sex), and year level involved (year 9 students only vs multiple or other years). Minimization is undertaken in StataCorp LLC Stata statistical software version 14.2 using the rct_minim procedure [36]. The pool of already available schools is sorted in random order using the Excel 2003 data analysis random number generator and entered into the minimization routine in ascending order using the factors specified above. Subsequent schools are assigned to an intervention arm using rct_minim in the order that they join the trial and provide complete information. As this trial uses a no-treatment comparator control group, participants and researchers are not blinded to the allocation assignment.

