### Sample Size

The target sample size for this trial is 1600. This calculation is based on detecting an effect size of 0.20, which is similar to that obtained in previous school-based depression intervention research [9]. The statistical power level is set at 0.8, alpha=.05 (2-tailed), whereas a correlation of 0.5 is assumed between the scores at baseline and endpoint. A design effect is calculated assuming an intraclass correlation of 0.02 and an average school sample of 300 students to allow for possible clustering effects. This estimate was derived from previous Australian school–based studies [9]. The estimated sample size also accommodates for a 20% attrition rate based on previous school-based trials [43]. To achieve the desired sample size and ensure representation from a range of different types of schools, the target is set at 16 schools with approximately 100 students participating per school.

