### Analysis

Data are collected using the Black Dog Institute electronic health platform. Data will be downloaded into Microsoft Excel and exported to SPSS Version 22.0 (SPSS Inc) for analysis. Primary analyses will be undertaken on an intention to treat basis, including all participants randomized, regardless of treatment received. Effectiveness of Smooth Sailing will be established by a change in the GHSQ scores between baseline and 12 weeks using a mixed-effects model repeated-measures analysis. The school will be included in analyses as a random effect to evaluate and accommodate clustering effects. In analyses of scaled secondary variables, methods comparable with those of the primary analysis will be used. An analysis of covariance will be conducted for the secondary outcomes of anxiety, depression, distress, functioning, mental health literacy, and barriers to help-seeking, controlling for baseline scores. To determine the effect of the intervention on help-seeking, 2 binary logistic regression analyses will be used. In model 1, the dependent variable will be help-seeking from adults at 12 weeks. The baseline result will be entered at step 1 in the model, with the study arm entered at step 2. In model 2, the dependent variable will be not seeking help at all at 12 weeks despite a need. The baseline result will be entered at step 1, with the study arm entered at step 2.

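### The two logistic models for help-seeking behavior list only baseline and arm, and the plan's general statement on a school random effect does not clearly cover them

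*Protocol article*

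**What the plan says.** The Randomization section makes the school the unit of allocation: "Schools are allocated to a single condition (cluster design) to avoid contamination and for administrative convenience". The Sample Size section expects outcomes to be correlated within schools: "A design effect is calculated assuming an intraclass correlation of 0.02".

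The Actual Help-Seeking Questionnaire section defines two secondary outcomes, both binary: whether help was sought from any adult, and whether no help was sought despite a need. For these the Analysis section states: "To determine the effect of the intervention on help-seeking, 2 binary logistic regression analyses will be used". For model 1 it continues: "The baseline result will be entered at step 1 in the model, with the study arm entered at step 2". For model 2: "The baseline result will be entered at step 1, with the study arm entered at step 2". Neither description names a school term, a mixed logistic model, GEE or a cluster-robust variance.

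Two other sentences of that section bear on the point. Directly after the mixed model for the General Help-Seeking Questionnaire (GHSQ) comes: "The school will be included in analyses as a random effect to evaluate and accommodate clustering effects". The next sentence is: "In analyses of scaled secondary variables, methods comparable with those of the primary analysis will be used".

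**The concern.** Students in one school share a counsellor, local protocols and whatever mental health activities the school runs, so their help-seeking may be correlated. A logistic regression with baseline and arm alone treats every student as independent, although the arm contrast rests on 16 planned schools or the 22 actually randomized. The standard error of the log odds ratio is then too small, the confidence interval too narrow, and a true null is rejected more often than 5% of the time.

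Help-seeking behavior is named in the trial's objectives, opens the secondary hypothesis and is the first key secondary outcome in Table 1. A falsely significant odds ratio would feed directly into the conclusion that the service changes what students do.

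**Working it through.** **1. Do the models contain a school term?** Three features of the Analysis section suggest not. The random-effect sentence follows the GHSQ model. The carry-over sentence is limited to scaled variables, and these two outcomes are yes/no. The logistic models are named as a different model type, with their terms given in order and school absent. Against this, the random-effect sentence speaks of analyses in general and has no stated limit. The text can be read both ways, and the specific description does not match the general one.

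**2. Inputs for the size of the effect.**
- ICC 0.02 (Sample Size). It was assumed for the sample-size calculation, not given for these outcomes.
- 1600 students and 20% attrition (Sample Size): 1600 × 0.8 = 1280 analysed.
- 16 planned schools (Sample Size): 1280 / 16 = 80 per school.
- 22 schools randomized, 10 and 12 (Results): 1280 / 22 ≈ 58 per school. This joins the target enrolment to the actual number of schools, because actual enrolment is not reported.
- Two-sided alpha 0.05: "The statistical power level is set at 0.8, alpha=.05 (2-tailed), whereas a correlation of 0.5 is assumed between the scores at baseline and endpoint".

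The plan states no error rate or precision for the binary outcomes, so there is no figure of its own to reproduce on this point.

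**3. Design-effect formula (no baseline adjustment).** DE = 1 + (m − 1) × ICC. The standard error is too small by a factor √DE, and the actual size of the test is 2 × [1 − Φ(1.96 / √DE)].

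| m | DE | √DE | Actual size of a nominal 5% test |
|---|---|---|---|
| 58 | 1 + 57 × 0.02 = 2.14 | 1.46 | 18.0% |
| 80 | 1 + 79 × 0.02 = 2.58 | 1.61 | 22.2% |

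At m = 80, other assumed ICCs give 9.7% (0.005), 14.3% (0.01) and 37.8% (0.05).

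**4. Simulation of the model as described.** The stated model adjusts for baseline, which absorbs part of any stable school effect, so the formula overstates the problem. Null trials were simulated with a school effect common to baseline and 12 weeks, and analysed by logistic regression on baseline and arm. The ICC is set on the latent scale: school variance = ICC / (1 − ICC) × π²/3, which is 0.067 at ICC 0.02. On the observed yes/no scale the correlation is smaller, very roughly 0.3 × 0.7 × 0.067 = 0.014 at 30% prevalence.

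| Setting, latent ICC 0.02 | 22 schools × 58 | 16 schools × 80 |
|---|---|---|
| 30% prevalence, strong student-level correlation (1500 trials each) | 7.9% | 10.1% |
| Separate simulation of the same model (2000 trials each) | 11.6% | 15.8% |

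The result depends on event rate and on how strongly a student's baseline and 12-week answers are linked, and the article gives neither. Varying both in a further check gave rates in about the same range. In the first setting with 16 × 80, the rate was 5.2% at ICC 0, 7.4% at 0.01 and 15.7% at 0.05. A school-level t-test on the same data stayed between 5.1% and 5.7%, so the excess comes from leaving school out.

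**The case against.** The strongest reply is that the random-effect sentence has no restriction. It refers to analyses in the plural, and where this section wants to limit a statement it does so in words. The logistic descriptions give an order of entry and do not say that nothing else enters. A condensed article may simply not repeat the school term. The authors plainly know about clustering, since they assume an ICC and put school in the primary model.

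This stands to the extent that a reader who infers that clustering will be ignored goes beyond the text. The article never says so. It does not remove the problem: the general sentence is followed at once by a carry-over limited to scaled variables, and then by models whose listed terms omit school. An analyst working from those descriptions would fit a single-level regression. Nor is this detail merely left to an analysis plan, because the article chose to name the models and their terms.

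It is also fair to object to the 18% to 22% figures as the expected error rate. They come from an unadjusted formula and a borrowed ICC, and the model adjusts for baseline. They serve only as an upper end at that ICC. Finally, these are secondary outcomes.

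**Conclusion.** The point holds as an unresolved conflict within the Analysis section. The two help-seeking models, as described, contain no school term, and the general random-effect sentence does not clearly reach them. If they are fitted as described, the direction of the error is certain under any positive ICC: standard errors too small and intervals too narrow.

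The size rests on assumptions. With an ICC near 0.02 and 58 to 80 analysed students per school, a nominal 5% test would run at roughly 8% to 16%, with 18% to 22% as the formula's upper end. A larger or smaller ICC moves these figures accordingly.

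A reader might also infer that the trial's main result is undermined. The document does not support that, because the GHSQ analysis includes school explicitly.

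**What to change.** State that both help-seeking models are mixed-effects logistic regressions with a random intercept for school and with baseline result and study arm as fixed effects. GEE clustered on school would also serve. In either case add a small-sample correction suited to about 16 to 22 schools, for example between-school degrees of freedom (22 − 2 = 20 for the schools randomized) or a corrected robust variance. Report the odds ratio with the interval from that model. Reword the random-effect sentence so that it names the outcomes it covers.

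The cost is a change of wording, a different SPSS procedure and wider confidence intervals. No new data are needed, and the Results section describes the analysis as still under way.

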**Secondary outcomes**					
	Actual Help-Seeking Questionnaire	Actual help-seeking behavior	Yes	Yes	Yes
	Generalized Anxiety Disorder Questionnaire	Generalized anxiety	Yes	Yes	Yes
	Center for Epidemiologic Studies Depression Scale—Child Version	Depressive symptoms	Yes	Yes	Yes
	Functioning	Functioning	Yes	Yes	Yes
	Distress Questionnaire-5	Psychological distress	Yes	Yes	Yes
	Barriers to Adolescents Seeking Help-Brief	Barriers to seeking help	Yes	No	Yes
	Mental Health Literacy and Stigma Scale	Mental health literacy and stigma	Yes	No	Yes

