### Secondary Outcome Measures

#### Actual Help-Seeking Questionnaire

The Actual Help-Seeking Questionnaire is used to assess help-seeking behavior [44]. Using the same sources presented in the GHSQ, participants are asked to report whether they have sought help for a mental health problem from these sources in the past 6 weeks (answered yes or no). Participants can also indicate if they have sought help from someone not listed. An additional question asks participants whether they have needed support for their mental health but did not seek help. The use of this questionnaire in youth has been well supported [30]. In this study, participants’ responses at baseline and 12 weeks posttest are categorized into a new variable named *help-seeking from adults*. Participants who have sought help from any adult source are categorized as yes, with those who have not categorized as no. This variable is then used as a secondary outcome for analyses, alongside the number of participants who report not seeking help at all despite having a need for mental health support.

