#### Distress Questionnaire-5

The Distress Questionnaire-5 (DQ5) is a brief, valid screener used for identifying those at risk of psychological distress in the general population [49]. The DQ5 consists of 5 items rated from never (1) to always (5). Total scores range from 5 to 25 and higher scores indicate greater psychological distress. It has been suggested that the DQ5 may be superior to the K6 and K10 in identifying increased risk for common mental disorders, with a screening cutoff point of 11 indicating the likely presence of a mental health condition [49].

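### The two help-seeking logistic models adjust only for a coarse yes/no baseline answer, so a consent-driven arm difference in baseline need would pass partly into the odds ratio; baseline DQ5 could be added

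*Protocol article*

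**What the plan says.** The Analysis section states: "To determine the effect of the intervention on help-seeking, 2 binary logistic regression analyses will be used". For model 1 (help-seeking from adults at 12 weeks) the terms are: "The baseline result will be entered at step 1 in the model, with the study arm entered at step 2". For model 2 (needing support at 12 weeks but not seeking it) they are the same: "The baseline result will be entered at step 1, with the study arm entered at step 2". A general sentence earlier in that section includes school as a random effect. It is not repeated for the logistic models, but I read it as covering them.

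The outcomes come from the Actual Help-Seeking Questionnaire, which asks "whether they have sought help for a mental health problem from these sources in the past 6 weeks". Model 1 is coded as follows: "Participants who have sought help from any adult source are categorized as yes, with those who have not categorized as no". Model 2 concerns "the number of participants who report not seeking help at all despite having a need for mental health support".

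Table 5 schedules the DQ5, CES-DC and GAD-7 at baseline, 6 weeks and 12 weeks. The DQ5 is described as a "brief, valid screener used for identifying those at risk of psychological distress". None of the three scores enters either logistic model.

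**The concern.** Both outcomes depend on whether the student has a problem at all, and the baseline answer separates students poorly on that. In model 1, a baseline no covers students without a problem and students who had one but went to no adult. In model 2, a baseline no covers students without need and students whose need was met. Conditioning on these answers leaves much of the variation in baseline need unadjusted.

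This matters if need differs between arms systematically, and the article describes a route by which it could:

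- Randomization: whole schools are allocated, without blinding. The minimization factors are socio-educational advantage, gender mix and year level, with no measure of need.
- Consent: students' signed consent is obtained on the day of the baseline assessment.
- Discussion (limitations): intervention students may be less likely to consent because that condition involves counsellor follow-up.
- The Intervention: follow-up is triggered by Step 3 or 4, or by a positive answer to PHQ-9 item 9, so it falls on students with high symptoms or such thoughts.

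Read together, these suggest fewer high-need students in the intervention arm. That direction is an inference; the article does not state it. The odds ratio would then fall below 1 in both models. In model 2 this would look like a benefit (less unmet need), and in model 1 like a harm (less help-seeking).

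**Working it through.** **No planned figure to reproduce.** The article gives no power or sample size for these two models. Its target of 1600 concerns the primary outcome and neither supports nor refutes this point.

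**Inputs from the article.** Target 1600 with 20% attrition: 1600 × 0.8 = 1280 analysed. There were 10 intervention and 12 control schools (Results), so 1280 / 22 ≈ 58 per school. As a check, the planned 16 schools give 1280 / 16 = 80 per school. The ICC is 0.02 (Sample Size).

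**Assumptions not in the article.** Intercept −1.2; stable person effect with SD 1; log-odds per SD of need (slope) 0.3, 0.6 or 1.0; systematic shift in baseline need of 0.1 or 0.2 SD; true log odds ratio 0 or 0.4.

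**Model.** At each time, logit P(yes) = −1.2 + slope × need + person effect + school effect, plus the treatment effect at 12 weeks. Each of 1,500 simulated trials was analysed with arm + baseline answer, and again with the need score added. Tests used school-clustered standard errors and t with (number of schools − 2) degrees of freedom. Monte Carlo error is about 0.6 points at 5%.

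**Step 1: no systematic shift, no effect.** Type I error is 4.7–5.1% with the planned terms and 5.1–5.3% with the score added.

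**Step 2: no shift, true log odds ratio 0.4.** Power for slopes 0.3, 0.6 and 1.0 goes from 63.0 to 63.5%, 60.5 to 61.9% and 57.7 to 59.6%. The SD of the arm log odds ratio does not fall; at slope 0.6 it rises from 0.145 to 0.150.

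**Step 3: systematic shift, no effect.** Some runs raised need in the intervention arm. By symmetry, lower need gives exp(−b), where b is the mean arm log odds ratio.

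| Schools | Slope | Shift (SD) | Planned terms: result | OR if need is lower | Rejection, planned | Rejection, score added |
|---|---|---|---|---|---|---|
| 22 | 0.3 | +0.2 | OR 1.04 | 1/1.04 = 0.96 | 6.6% | about 5–6% |
| 22 | 0.6 | +0.2 | OR 1.08 | 1/1.08 = 0.93 | 9.1% | about 5–6% |
| 22 | 1.0 | +0.2 | OR 1.13 | 1/1.13 = 0.88 | 12.4% | about 5–6% |
| 22 | 1.0 | −0.2 | b = −0.120 | exp(−0.120) = 0.89 | 11.7% | 5.3% |
| 16 | 0.6 | −0.2 | b = −0.080 | exp(−0.080) = 0.92 | 8.7% | 5.7% |
| 22 | 1.0 | +0.1 | b = 0.061 | exp(−0.061) = 0.94 | 6.7% | 5.5% |
| 16 | 0.6 | +0.1 | b = 0.040 | exp(−0.040) = 0.96 | 5.2% | 4.6% |

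For slope 0.3 and shift 0.1, halving ln(1.04) = 0.039 gives about 0.020, and exp(−0.020) = 0.98. With the score added, the mean odds ratio is about 1.00. A simpler simulation with independent students, slopes 0.5–1.1 and a baseline-to-12-week distress correlation of 0.6–0.7 gave 0.92–0.96 and 5–10% for a 0.2 SD shift.

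**Step 4: how large is 0.2 SD?** Take normally distributed need. The top quarter has mean 1.271 and the rest −0.424. If the top quarter consents at half the rate of the others in intervention schools only, the mean is (0.125 × 1.271 − 0.75 × 0.424) / 0.875 = −0.18 SD. At three-quarters of the rate it is (0.1875 × 1.271 − 0.75 × 0.424) / 0.9375 = −0.08 SD. So 0.2 SD is a strong scenario and 0.1 SD a moderate one.

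**Limit of the check.** The score added in Steps 1 to 3 is the same need variable that generates the outcome. Full removal of the bias is therefore a best case; a fallible DQ5 would remove less.

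**The case against.** Adjusting a binary outcome for its own baseline value is conventional, and further covariates are often left to an analysis plan, which is not shown. This largely stands: the models are valid and the point is an improvement. The article does, however, spell out the covariates term by term, so the choice can be reviewed.

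Two stronger readings are tempting, and neither is supported. A reader might infer that any imbalance in need, including a chance one, would be mistaken for a service effect. Chance imbalance is already within the 5% error rate once school clustering is modelled (Step 1). A reader might also infer that leaving out the score costs precision. In logistic regression the standard error of the arm log odds ratio does not shrink when a prognostic score is added, and Step 2 shows almost no gain in power. Nor are the models bare of everything but the baseline answer and arm, given the general sentence on school.

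The size of any systematic shift is assumed, and the article says only that consent may differ. This stands and limits the weight of the point. It is also fair that model 2's baseline item is itself a report of unmet need, and that reluctance to see a counsellor may be captured better by past help-seeking than by distress. Finally, the Discussion reports concern that students may not disclose symptoms openly to a Web-based service. If disclosure at baseline differed by arm, adjusting for DQ5 could add bias of its own. That is a reason to show both models.

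**Conclusion.** The point holds in a limited form. Both models condition on a coarse proxy for need, in a design where the article's own account makes a systematic arm difference in need plausible. For an assumed shift of 0.1 to 0.2 SD, the odds ratio under no effect is about 0.92 to 0.98 for slopes up to 0.6. At slope 1.0 and 0.2 SD it reaches about 0.89, and the 12% type I error belongs to that corner; elsewhere the error is about 5 to 9%. Adding a score that captures need returns the odds ratio to about 1.00 and the error to about 5 to 6%. These figures rest on the assumed slope, shift and person effect, on an ICC of 0.02, and on clustering being handled. The documents do not show that an imbalance occurred. The outcomes are secondary, so this is a worthwhile refinement and does not invalidate the analysis.

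**What to change.** In both logistic models, enter the baseline DQ5 total as a continuous covariate at step 1 with the baseline answer, then the arm at step 2, and keep school as a random effect. Name this one score in advance so that the covariate is not chosen from the data. The Results section says analysis is under way. If outcomes by arm have already been seen, leave the planned models as they are and report the DQ5-adjusted versions beside them, labelled as a sensitivity analysis.

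The cost is one covariate in two models, with no new data. The odds ratio becomes conditional on distress as well as on the baseline answer, any missing baseline DQ5 totals need a stated handling rule, and only selection captured by the DQ5 is removed.

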### Dissemination Policy

A summary of the results will be emailed to all participants who request this on their consent form. The results summary will also be published on the Black Dog Institute website. School reports, consisting of the mean aggregate scores for the measures, will be prepared and shared with the school at completion of the data collection period. The primary and secondary outcomes analysis will be prepared for academic publication and presentations. A final report will also be submitted to the funding body. In all documents, participants will not be individually identifiable with data presented at the aggregate level.

